### Criteria for discontinuing or modifying allocated interventions {11b}

The FiO_2_ will be adjusted to 40% and 80% in the L and H cohorts, respectively. Should the intraoperative oxygen saturation of the participants in the L cohort decline to < 94%, while the PEEP remains at 30 cm H_2_O, at a duration of ≥ 30 s, without an improvement in the oxygen saturation, the oxygen concentration will be increased to 80%.

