**Methods:**

This multicenter, prospective, parallel-cohort, randomized controlled clinical trial will include 1098 older adult participants aged ≥ 65 years old undergoing laparoscopic gastrointestinal surgery, from 16 clinical trial sites across China. Participants will be randomized, as per a 1:1 ratio to two cohorts, the “L” and “H” cohorts, to receive low FiO_2_ (40%) and high FiO_2_ (80%) levels, respectively. The primary outcome measure is the 48-h postoperative oxygenation index between the two cohorts. The secondary outcome measures include the other blood gas analysis results, PPCs within 7 days, and 30-day mortality rate.

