### Intervention description {11a}

Preoperatively, the participants in both cohorts will fast for 8 h and not use any sedatives or analgesics. On arrival at the ward/operating room, the data will be verified, and standard monitoring of the systolic and diastolic blood pressure, mean arterial pressure, pulse rate, electrocardiogram, blood oxygen saturation, entropy index, or bispectral index (BIS) will be conducted. Simultaneously, venous access will be obtained and maintained at a rate of 10–20 mL/kg/h. The total fluid volume will not exceed 50 mL/kg, to ensure intraoperative hemodynamic stability.

Intraoperatively, the same protocol will be used for anesthesia induction: etomidate 0.3 mg/kg or propofol 1.5–2 mg/kg, sufentanil 0.3–0.5 μg/kg, cisatracurium besylate 0.2 mg/kg, or rocuronium bromide 1 mg/kg, respectively. Anesthesia methods, including combined intravenous and inhalation anesthesia, total intravenous anesthesia, inhalation anesthesia, and reasonable use of vasoactive drugs, can be used intraoperatively.

The ventilator will be connected to the participant after a successful tracheal intubation. All participants will be ventilated using lung-protective ventilation, which includes VCV, PCV, and PCV-VG.

The tidal volume will be set at 6–8 mL/kg, which has been calculated, based on the ideal body weight, using the following formulae:For males: 50 + 0.91 × [height (cm)—152.4].For females: 45.5 + 0.91 × [height (cm)—152.4].

Moreover, the positive end-expiratory pressure (PEEP) and inspiratory/expiratory ratio will be maintained at 6–8 cm H2O and 1:2, respectively, with regular lung recruitment maneuvers. The ventilation rate will be adjusted, according to the intraoperative end-expiratory carbon dioxide, which will be maintained at 35–50 mm Hg.

The depth of anesthesia will continuously be adjusted, according to the entropy index, BIS value, or minimum alveolar concentration (MAC) value of the end-expiratory anesthetic gas. The entropy index and BIS value or MAC value of the end-expiratory anesthetic gas will be maintained at 40–60 or 0.7–2.6, respectively.

Intraoperative and perioperative information, adverse events (AEs), and serious adverse events (SAEs) will be recorded. Perioperative data includes the duration of the anesthesia and surgery, use of different types of anesthetics, volumes of fluids administered intraoperatively, and administration of postoperative analgesics and anticholinergic drugs.

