## Assignment of interventions: blinding

### Who will be blinded {17a}

Due to the nature of the study, anesthesiologists will not be blinded to the intervention protocol. Trial participants, outcome assessors, and data analysts will be blinded. To reduce potential bias, data collectors will be divided into two different teams: (1) anesthesiologists on duty in the operating room on the same day, in addition to postanesthetic care unit (PACU) staff, who will participate in the calculation and evaluation of the results, and (2) blinded principal investigator (PI) and co-investigator, statistician, and data collection and outcome evaluation personnel, which includes those who will provide care and evaluate participants in the ward pre- and postoperatively.

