## Data collection and management

### Plans for assessment and collection of outcomes {18a}

Each site will administer anesthesia, according to their institutional guidelines. Medication type, dosing, and additional analgesics administered, as per each site’s anesthesia protocol, will be documented, in detail, in the case report form (CRF). A qualified and experienced anesthesiologist will be required to complete the CRF.

Prior to study initiation, researchers will receive training on the study protocol, according to the principles of GCP for clinical trials.

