### Methods for additional analyses (e.g., subgroup analyses) {20b}

#### Analysis sets

The enrolled set will consist of all participants who provided informed consent and were added to the study database.The full analysis set (FAS) describes the analysis set, which is as complete and close as possible to the intention-to-treat ideal of including all randomized participants, who have undergone ≥ 1 efficacy assessment, post-randomization.The per-protocol set (PPS) defines a subset of the participants in the FAS who are more compliant with the protocol and have undergone ≥ 1 efficacy assessment, post-randomization. Participants with protocol deviations will be excluded from this analysis.

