### Methods in analysis to handle protocol nonadherence and any statistical methods to handle missing data {20c}

In the analysis of the primary outcome measure, missing values within the FAS will be excluded.

The analysis of the primary, secondary, and safety outcome measures will be conducted, based on the intention-to-treat principle. Thus, participants will be analyzed, according to either of the intervention cohorts to which they were randomized, and all participants will be included in the analysis, regardless of whether they were assigned to the intervention or not (the FAS).

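### The rule for raising oxygen from 40% to 80% in the L cohort requires a PEEP of 30 cm H2O, although the protocol maintains PEEP at 6–8 cm H2O for everyone

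*Protocol article*

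**What the plan says.** Section 11b of the protocol article (criteria for discontinuing or modifying allocated interventions) sets FiO2 at 40% in the L cohort and 80% in the H cohort. It then gives one exception, for the L cohort only. If intraoperative saturation falls below 94% "while the PEEP remains at 30 cm H_2_O, at a duration of ≥ 30 s", and saturation does not improve, oxygen is raised to 80%.

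Section 11a (intervention description) fixes the ventilation for both cohorts. "All participants will be ventilated using lung-protective ventilation", and "the positive end-expiratory pressure (PEEP) and inspiratory/expiratory ratio will be maintained at 6–8 cm H2O and 1:2, respectively, with regular lung recruitment maneuvers". It gives neither a pressure nor a duration for those maneuvers.

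The statistical methods in section 20a list intraoperative PEEP and pulmonary re-expansion as two separate model covariates.

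**The concern.** The exception depends on a PEEP value that the protocol's own ventilation settings do not allow. Read literally, it has two possible meanings, and neither is acceptable:

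- PEEP stays at 6–8 cm H2O as section 11a requires. The condition is then never met, and the rule never permits more oxygen.
- PEEP is taken to 30 cm H2O to satisfy the rule. A desaturating patient aged 65 or over is then exposed to a pressure far outside the prescribed lung-protective setting before oxygen is raised.

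The rule does two jobs. It is the oxygen rescue for the L cohort. It also decides when an L participant may receive the H cohort's FiO2, which is the very contrast under test.

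Anesthesiologists who reject the literal wording have to supply their own rule. Patients come "from 16 clinical trial sites across China", and "anesthesiologists will not be blinded to the intervention protocol". Rescue and crossover could therefore be handled differently from site to site.

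**Working it through.** The article states no derived figure to reproduce here. The check is a comparison of sections, with simple arithmetic for the size of the gap.

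**Inputs**

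| Item | Value | Source |
|---|---|---|
| Maintained PEEP, all participants | 6–8 cm H2O | Section 11a |
| Recruitment maneuvers | regular; no pressure or duration given | Section 11a |
| Saturation trigger, L cohort | below 94% | Section 11b |
| PEEP in the rule | 30 cm H2O for at least 30 s | Section 11b |
| Action | FiO2 raised to 80% | Section 11b |
| Planned total, 1:1 allocation | 1098 | Abstract, Methods; section 14 |

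**Size of the conflict**

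- Difference: 30 − 8 = 22 and 30 − 6 = 24, so the rule's PEEP is 22–24 cm H2O above the maintained range.
- Ratio: 30/8 = 3.75 and 30/6 = 5, so it is 3.75 to 5 times the maintained PEEP.

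**Who is covered**

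- 1098/2 = 549 participants planned for the L cohort. This is the number to whom the rule applies, not the number expected to trigger it. The article gives no rate of intraoperative desaturation, so that second number cannot be estimated.

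**Can the two sections be reconciled?**

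1. Section 11b speaks of PEEP remaining at 30, which describes a continuing setting. Section 11a describes a continuing setting of 6–8. Both cannot be true of the same patient at the same time.
2. No section provides for raising PEEP above 6–8, even briefly.
3. A pressure of 30 cm H2O paired with about 30 s looks like a recruitment maneuver, and section 11a mentions such maneuvers. This makes a mislabelled airway pressure the most likely explanation. It remains an inference, since no section gives that pressure or links the maneuver to the rule.
4. Section 20a treats PEEP and re-expansion as different variables, so the protocol does not use PEEP as a general term for a recruitment maneuver.
5. Even on the charitable reading, section 11b names the wrong parameter, does not instruct anyone to perform a maneuver, and does not say that PEEP returns to 6–8 afterwards.

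**The case against.** The best defence is that any anesthesiologist will recognise a recruitment maneuver. The stated duration suggests a short step rather than a setting, and a short step on desaturation can coexist with a maintained range of 6–8. Staff are experienced and trained on the protocol beforehand (section 10), and the full protocol behind the article may describe the maneuver. On this view the fault is one wrong word.

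Much of that is fair. The intended meaning is probably as described, and few anesthesiologists would follow the literal text. But the article prints the rule with numbers, so this is an incorrect statement rather than a detail left to a longer document.

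Other points on that side, and what stands of them:

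- **Site variation is not demonstrated.** Correct. Section 18a does say "Each site will administer anesthesia, according to their institutional guidelines", but the sentence after it concerns medication, dosing and analgesics, so it is weak evidence about oxygen rescue. Knowledge of the allocation is also unavoidable for a rule confined to one cohort. Differing practice is a possibility, not a finding.
- **Center is stratified at randomization and included in the models.** This limits confounding by site. It does not make the crossover rule uniform.
- **Few may need the rule.** Eligibility requires a preoperative saturation of at least 94% and excludes severe pulmonary dysfunction and BMI above 30 kg/m². The number may be small, but it is unknown.
- **Participants can be withdrawn if continuing may harm them.** Withdrawal is a safeguard, but it does not say when to raise oxygen.

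**Conclusion.** The concern holds: the rescue and crossover rule in section 11b is wrong as written. Its PEEP of 30 cm H2O is 22–24 cm H2O above the range maintained for all participants, and nothing else in the article reconciles the two.

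The consequences are limited. On the analysis side, "participants will be analyzed, according to either of the intervention cohorts to which they were randomized", so a participant raised to 80% stays in the L cohort for the intention-to-treat comparison. The sample-size calculation and alpha do not depend on the rule. A secondary effect falls on the per-protocol set: "Participants with protocol deviations will be excluded from this analysis", and an unclear rule leaves it unclear which FiO2 increases were permitted and which were deviations. No effect on the primary result has been shown.

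The conclusion that the two sections conflict needs no assumption. That the 30 is a recruitment-maneuver airway pressure is an inference for the investigators to confirm. The point should be fixed because it concerns patient safety and the integrity of the treatment contrast, and the correction is nearly free.

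**What to change.** Replace the sentence in section 11b with wording along these lines: if intraoperative saturation in the L cohort falls below 94%, perform a recruitment maneuver at an airway pressure of 30 cm H2O held for about 30 s; return PEEP to 6–8 cm H2O; if saturation has not improved, raise FiO2 to 80%. The investigators should confirm the pressure and the duration, since the article does not establish either as the intended maneuver setting.

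Send the wording to the 16 sites as a clarification. If enrolment has already closed (the trial status section estimates an end date of 31 December 2025), correct the text and report which reading the sites used, so that increases to 80% can be interpreted.

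The cost is one sentence and one notice to sites. Sample size and analysis do not change.

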### Withdrawal from study

Participants will be withdrawn from the study, if any of the following circumstances arise:The participant has voluntarily withdrawn consent from the study.Continuing in the trial will may be harmful to the health of the participant.The trial records cannot be completed, and the research investigator regards the participant as no longer able being to continue in the trial.AEs related to the trial intervention occur.Factors posing a risk are considered by the Trial or Advisory Committee.The rationale for a participant’s withdrawal from the study will be documented in the “Withdrawal/Change of Status” table.

### Strategies to improve adherence to interventions {11c}

We plan to implement the following measures to enhance patient compliance:

Thoroughly explain to patients that both oxygen concentrations are clinically established and medically acceptable methodsArrange for arterial blood sampling postoperatively to be performed by experienced anesthesiologists and coordinate with the ward staff to incorporate it into routine postoperative testing

### Relevant concomitant care permitted or prohibited during the trial {11d}

N/A. There are no restrictions on relevant concomitant care.

### Provisions for posttrial care {30}

N/A. Both oxygen concentrations are clinically safe for completing surgical procedures and are not expected to cause harm to participants. Therefore, no compensation will be provided.

### Outcomes {12}

#### Primary outcome

The primary outcome measure is the comparison of the 48-h postoperative oxygenation index between the two cohorts. This will be derived from arterial blood gas sampling and analysis, in addition to the FiO_2_ 48th h postoperatively.

#### Secondary outcomes

The results of blood gas analyses including PH value and PaCO_2_ lactic acid between the two cohorts, within 48 h postoperativelyThe time of oxygen inhalation, the inspired oxygen concentration, and the rate of oxygen uptakeThe 7-day pulmonary and 30-day mortality rate between the two cohorts

### Participant timeline {13}

The enrollment, interventions, assessments, and visits for participants are shown in Fig. 2.

**Fig. 2 Fig2:**
[figure not shown]
Enrollment, interventions, assessments, and visits for participants

### Sample size {14}

This randomized controlled trial aimed to examine the effect of varying intraoperative oxygen concentrations on PPCs. This study is a superiority trial in which the optimal effect threshold has been set. Based on a preliminary experiment, 10 samples were collected each group, and the values of oxygenation index were expressed as mean ± standard deviation: 384 ± 85 mmHg for 40% group and 340 ± 60 mmHg for 80% group. This study was designed as a superiority trial, with a clinically significant difference defined as an increase in oxygenation index by at least 30 (10% of 300 acute lung injure oxygenation index) in favor of 40% group compared to 80% group. The pooled standard deviation was estimated to be 74 mmHg. The sample size required for each group to achieve a significant difference, with a one-sided *α* = 0.025 and *β* = 0.20. The minimum sample size required for each group was approximately 439, with a total of 1098 samples needed for both groups, considering a dropout rate of 20%.

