## Statistical methods

### Statistical methods for primary and secondary outcomes {20a}

The oxygenation index data for the two cohorts will be collected, based on a preliminary experiment. The oxygenation index values will be presented as means and standard deviations.

The Student’s *t*-test will be used to assess the disparities between the two cohorts for continuous outcome variables adhering to a normal distribution. In cases of non-normal distribution, the Mann–Whitney test will be used. Categorical data will be analyzed, using the chi-squared or Fisher’s exact tests. These tests are one-sided, and statistical significance will be set at *p* < 0.025. The parameters will be computed and displayed, including approximations and a 97.5% confidence interval.

The primary and secondary outcome indicators will be evaluated using linear and generalized linear mixed-effects models.

A linear mixed-effects model was employed to analyze the primary outcome measures (oxygenation index and quantitative variables). The model included patient baseline data (age, gender, BMI, and prior SARS-CoV-2 infection history), intraoperative characteristics (anesthesia duration, intraoperative crystalloid volume, intraoperative colloid volume, surgical duration, surgical position, pneumoperitoneum pressure, intraoperative PEEP, occurrence of pulmonary re-expansion, intraoperative ventilator tidal volume, and airway platform pressure), and center and group factors.

For quantitative secondary outcome measures—including postoperative PACU oxygen duration, 24-h and 48-h oxygen therapy duration, and postoperative blood gas parameters (pH, partial pressure of carbon dioxide, and lactate) at 48 h—linear mixed-effects models were employed. The model included patient baseline characteristics (age, gender, BMI, and prior SARS-CoV-2 infection history) and intraoperative parameters (anesthesia duration, intraoperative crystalloid volume, colloid volume, surgical duration, surgical position, pneumoperitoneum pressure, intraoperative PEEP, occurrence of pulmonary re-expansion, and ventilator tidal volume), along with center and group factors.

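### The 439 per group is sized for superiority beyond a 30 mmHg margin, but the analysis section puts that margin into no null hypothesis or success rule

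*Protocol article*

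**What the plan says.** Protocol article, Sample size {14}. The design is described thus: "This study is a superiority trial in which the optimal effect threshold has been set". The threshold follows, "with a clinically significant difference defined as an increase in oxygenation index by at least 30 (10% of 300 acute lung injure oxygenation index", in the direction of the 40% group. The planning values come from a pilot with 10 participants per group: "384 ± 85 mmHg for 40% group and 340 ± 60 mmHg for 80% group". "The pooled standard deviation was estimated to be 74 mmHg". The error rates are given "with a one-sided *α* = 0.025 and *β* = 0.20". The result is: "The minimum sample size required for each group was approximately 439, with a total of 1098 samples needed for both groups", after allowing for 20% dropout.

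Protocol article, Statistical methods {20a}. Student's t-test "will be used to assess the disparities between the two cohorts for continuous outcome variables adhering to a normal distribution", with Mann-Whitney as the substitute under non-normality. These simple tests, together with the chi-squared and Fisher tests for categorical data, are one-sided at p < 0.025, and a 97.5% confidence interval is promised. The section then says: "A linear mixed-effects model was employed to analyze the primary outcome measures (oxygenation index and quantitative variables"), with group, centre and a list of covariates. The 30 mmHg does not appear in this section.

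The Objectives and Outcomes sections frame the primary question only as whether the oxygen level affects the 48-hour index and as a comparison of the two cohorts.

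**The concern.** A sample size and a test belong together: the power statement holds only for the hypothesis behind the calculation. Here the calculation appears to answer whether 40% oxygen is better by more than 30 mmHg. The analysis section, read in the ordinary way, answers whether it is better at all.

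What counts as a positive trial depends on which question is meant. If the ordinary reading is followed, 40% oxygen could be declared superior on a difference well below the one the protocol itself calls clinically significant, and the stated 80% power would describe a test that is never run.

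**Working it through.** **Inputs**, all from Sample size {14} except the 1:1 allocation (Sequence generation {16a}): pilot means 384 and 340 mmHg; pilot SDs 85 and 60; planning SD 74; threshold 30 mmHg; one-sided alpha 0.025 (z = 1.960); power 80% (z = 0.842); dropout 20%.

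**1. Planning SD.** √((85² + 60²)/2) = 73.57, stated as 74.

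**2. The plan's own figure.** Expected difference 384 − 340 = 44. Taking 30 as a margin, the net difference is 44 − 30 = 14 mmHg.

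n per group = 2 × (1.960 + 0.842)² × 74² / 14² = 438.6, so 439.

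Dropout: 439/0.8 = 548.75, so 549 per group and 1098 in total. Both stated figures match exactly. (A t-based calculation gives 440. The unrounded SD of 73.57 gives 434.)

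**3. The same inputs with a null of zero.**

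| Difference to detect | n per group |
|---|---|
| 30 mmHg | 2 × 2.802² × 74² / 30² = 95.5, so 96 |
| 44 mmHg | 2 × 2.802² × 74² / 44² = 44.4, so 45 |

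Neither is near 439. For 30 mmHg against zero, 439 is about 4.6 times the required number (439/96).

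**4. Smallest significant observed difference**, unadjusted, SD 74, 439 per group.

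SE = 74 × √(2/439) = 4.99 mmHg; 1.96 × SE = 9.8 mmHg.

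- Null of zero: an observed difference of about 9.8 mmHg suffices.
- Null of at most 30 mmHg: about 30 + 9.8 = 39.8 mmHg is needed.

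If all 549 per group were analysed, SE = 4.47 and the two cut-offs become 8.8 and 38.8 mmHg.

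**5. Chance of success under each rule**, unadjusted, 439 per group, from Φ((true − null)/SE − 1.96).

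| True difference (mmHg) | Against 0 | Against 30 |
|---|---|---|
| 20 | 98% | under 0.01% |
| 30 | over 99.9% | 2.5% |
| 35 | over 99.9% | 17% |
| 40 | over 99.9% | 52% |
| 44 | over 99.9% | 80% |

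**6. Confidence interval.** A one-sided 97.5% lower limit is the lower end of a two-sided 95% interval, with half-width 9.8 mmHg. A two-sided 97.5% interval has half-width 2.241 × 4.99 = 11.2 mmHg. The article does not say which it means, and only the first matches the sized test.

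**The case against.** The strongest reply is that no null of zero is written anywhere. The analysis section names families of tests. A t-test or a mixed-model contrast can be run against 30 as easily as against 0, and even Mann-Whitney can be, by subtracting 30 from one arm, which then tests a location shift. The sample size section can be read as giving the hypothesis and the analysis section as giving the method, with the formal null left to a fuller document. One-sided testing and a confidence interval both fit a margin design. This stands in part: the zero null is the default reading of an unshifted test, not a statement in the text. It does not remove the problem. The article gives both a sample size and its tests, and nothing in it connects the threshold to the decision.

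It can also be said that 30 mmHg is only an aid to interpretation and that the reported interval will show whether it is excluded. The interval would indeed help the reader, but on that view 439 cannot be derived from the stated inputs.

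A reader might further infer that three competing analyses give several chances of success at 0.025. The text does not support this. The t-test and Mann-Whitney test are alternatives for continuous outcomes in general, the mixed model is the one tied to the oxygenation index, and the 0.025 sentence follows only the simple tests. What remains is that the article does not say outright that the model decides.

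Finally, the figures above are unadjusted. The planned model adjusts for centre and many covariates, so its standard error and both cut-offs would differ.

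**Conclusion.** The inconsistency is real and bears on the primary success criterion. Among the readings checked, 439 and 1098 follow only from superiority by a 30 mmHg margin with an expected 44 mmHg. The analysis section carries that margin into no test, confidence limit or success rule.

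Run as they are ordinarily run, the named tests would succeed at about 9.8 mmHg, roughly one third of the protocol's own threshold, instead of about 39.8 mmHg. These cut-offs assume SD 74, 439 analysed per group and no covariate adjustment. Adjustment would move both cut-offs but would leave the 30 mmHg gap between the two null hypotheses.

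A reader might infer that the protocol has chosen a test against zero. It has not said so, and an analysis plan not shown here could state the shifted null. The conclusion is narrower: the sample size and the tests, as this article states them, do not address the same hypothesis, and one of the two sections must change. Testing against zero would not inflate the type I error for a null of zero. The harm lies in what a significant result would be taken to show.

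**What to change.** **If the margin is intended**, in {20a}:

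- State the null hypothesis: mean(40%) − mean(80%) ≤ 30 mmHg.
- Confirm the group contrast from the linear mixed model as the single deciding primary analysis, with the t-test or Mann-Whitney comparison supportive only. This point asks for no change to the covariate list.
- Declare superiority only if the one-sided 97.5% lower limit, which is the lower limit of a two-sided 95% interval, exceeds 30 mmHg. Reword the stated 97.5% confidence interval to match.
- Report the comparison with zero as secondary.

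**If a test against zero is intended**, restate {14}: 96 per group (120 after 20% dropout, 240 in total) gives 80% power for 30 mmHg, and 439 per group gives over 99.9%. Say also that a significant result alone does not show a clinically significant difference.

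**Cost.** Wording only, and no extra participants. The first option makes the success criterion stricter: power is 80% only if the true difference is 44 mmHg, and it falls to 52% at 40 mmHg in the unadjusted calculation. The change must be made before unblinded data are seen. The article gives an estimated end date of 31 December 2025 and plans interim analyses at 50% and 75% of the sample. It does not show whether comparative data have already been viewed, so the amendment should record that status.
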